#### Clinical outcomes—primary outcome

The primary outcome will be the incidence of SSI—measured by total ASEPSIS score ≥ 21 [19]—within 30 days of surgery, or as defined by the CDC definition of SSI [1, 20].

#### Secondary outcomes

Secondary outcomes will be:The incidence of SSI—total ASEPSIS score ≥ 21 or SSI as defined by CDC definitions—at 90 days for implant patients only (as per the CDC definition for SSI in implant-involving surgery)Satisfactory healing—total ASEPSIS score ≤ 10—at 30 days post-surgery for non-implant surgery and implant patientsSatisfactory healing—total ASEPSIS score ≤ 10—at 90 days for implant patients onlyQuality of life: using EurolQol 5 Domains (EQ-5D-3 L) and Short Form 36 (SF-36) v2 questionnaires at 5–7 days, 30 ± 3 days, 3 months ± 7 days, and 6 months ± 7 days.Time to return to normal activity/work (measured in working days between the day of surgery and the day the patient returned to work).Resource use—primary care visits, requirement for antibiotics, readmission, re-intervention within 30 days and 6 months.30-day mortality.

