**Methods:**

Patients undergoing clean or clean-contaminated vascular surgery will be randomised to have their surgical wounds dressed with a DACC-coated dressing or a non-coated occlusive absorbent post-operative dressing. All other aspects of their peri-operative care will be standardised or carried out in line with hospital policy. Wound assessments will be carried out between day 5–7, day 30 (± 3 days) and 6 months post-operatively (± 7 days) by a blinded assessor using the ASEPSIS scoring tool. Quality of life data using EQ-5D and SF-36, resource use and mortality data will also be collected. This feasibility trial will dictate the conduct of a full-scale trial through the collection of data on recruitment and retention rates, and fitness-for-purpose of the follow-up arrangements.

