### Study visits

Following screening and informed consent, a baseline visit will take place to record demographic data and medical history, prior to randomisation. Study visits will take place between post-op days 5 and 7, at post-op day 30 and at 6 months. Patients will be contacted both by post and telephone when arranging follow-up in order to maximise retention. At the study visits, information such as antibiotic use, length of hospital stay, visits to the general practitioner, dressing changes/number of dressings used and return to work or daily activities will be recorded by a non-blinded study nurse or doctor. Patients will be deemed to have returned to normal activities if they have returned to work (if they are of working age) or if they have returned to their pre-operative activity levels. In particular, patients will be asked if they have returned to driving, exercise or previous levels of social activity.

The same individual will remove the dressing in situ and dispose of it in an opaque bag. A second assessor, blinded to the dressing type, will be invited into the room in order to score the wound on the ASEPSIS scale. This will be recorded in the CRF. With the dressing removed, anonymous photographs will be taken of the wound, to be reviewed by an assessor not involved in trial recruitment or follow-up and used for the standardisation of ASEPSIS scores between participants. With the blinded assessor out of the room, the first study nurse or doctor will replace the dressing. Postal quality of life questionnaires will be sent to participants at 3 months and 6 months. Table 1 outlines the schedule of assessments.

**Table 1 Tab1:** Schedule of assessments (SPIRIT figure)

Visit	1	2	3	4	5	–	–
	Screening	Baseline assessment	Day 0- day of surgery	Day 5–7 post op	Day 30 post op ± 3 days	3 Months post-op ± 7 days	6 Months post-op ± 7 days
Screening questionnaire	X						
Patient information sheet	X						
Informed consent		X					
Baseline questionnaire		X					
SF-36		X		X	X	X	X
EQ-5D-3 L		X		X	X	X	X
GP letter		X					
RANDOMISATION FORM			X				
HPA surgical wound healing post discharge questionnaire					X		x
Clinical review of wound				X	X		X

*SF36* short form 36 utility, *EQ*-*5D* EuroQoL 5 domain utility index, *HPA* health protection agency

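### Two 90-day outcomes in implant patients rely on an ASEPSIS score, but no wound review or wound questionnaire is scheduled at 3 months

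*Protocol article*

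**What the plan says.** Under Secondary outcomes, the protocol article sets two outcomes in implant patients at 90 days:

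- SSI, met by a total ASEPSIS score of 21 or more or by the CDC definition, "at 90 days for implant patients only (as per the CDC definition for SSI in implant-involving surgery".
- Satisfactory healing, met by a total ASEPSIS score of 10 or less, again "at 90 days for implant patients only".

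The follow-up arrangements appear in three places:

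- Abstract, Methods: "Wound assessments will be carried out between day 5–7, day 30" (± 3 days) and 6 months (± 7 days).
- Study visits text: "Study visits will take place between post-op days 5 and 7, at post-op day 30 and at 6 months". The contact in between is by post: "Postal quality of life questionnaires will be sent to participants at 3 months and 6 months".
- Table 1: the row "Clinical review of wound" is marked at day 5–7, day 30 and 6 months. The row "HPA surgical wound healing post discharge questionnaire" is marked at day 30 and 6 months. The 3-month column is marked only for SF-36 and EQ-5D-3L.

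ASEPSIS is scored in person. An unblinded team member removes the dressing, and a second, blinded assessor "will be invited into the room in order to score the wound on the ASEPSIS scale". The photographs used to standardise scores are taken on the same occasion.

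**The concern.** Both outcomes name a time at which the plan collects no wound data. A team following Table 1 would reach the analysis with no 90-day ASEPSIS score for any implant patient.

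The Introduction gives 90 days as the CDC window when an implant is left in place, so the period left without wound review is the extra period that sets implant surgery apart. Infections arising after the day-30 visit would enter the comparison only if they happened to leave a trace elsewhere. Dressing type cannot be masked from patients or ward staff, and the plan relies on a blinded assessor to limit bias. Whatever replaces the missing score would lack that protection.

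The pilot is also meant to show whether the outcome measures and follow-up arrangements suit a full trial. As written, it would not try out a 90-day wound assessment at all.

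**Working it through.** The plan gives no figure for the 90-day outcomes. Its sample-size calculation is based on the primary outcome and does not bear on this point. The check sets outcome times against data-collection times.

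**Sources of wound data by time point (Table 1, with the Abstract and Study visits text)**

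| Time point | Wound review with ASEPSIS | HPA wound questionnaire | Quality-of-life forms |
|---|---|---|---|
| Day 5–7 | yes | no | yes |
| Day 30 ± 3 | yes | yes | yes |
| 3 months ± 7 days | **no** | **no** | yes, by post |
| 6 months ± 7 days | yes | yes | yes |

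Wound reviews or wound questionnaires scheduled at 3 months: 0. The Abstract and the prose agree with the table, so a table damaged in extraction does not explain the gap. No separate schedule for implant patients is described.

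**Distance from day 90 to the nearest reviews**

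- Latest possible day-30 review: 30 + 3 = day 33. Gap to day 90: 90 − 33 = 57 days.
- Earliest possible 6-month review, assuming 6 months is about 182 days: 182 − 7 = day 175. Gap after day 90: 175 − 90 = 85 days.

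These are the smallest gaps the visit windows allow.

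**What each outcome component can draw on**

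| Component | Source at or near day 90 |
|---|---|
| Healing, ASEPSIS 10 or less | none |
| SSI, ASEPSIS 21 or more | none; if incidence is counted cumulatively, scores up to day 33 contribute and days 34 to 90 add nothing |
| SSI, CDC definition | no scheduled source; partial recovery from records collected for other purposes |

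The records in the last row are antibiotic use and general-practitioner visits taken at study visits, the resource-use items (which include readmission and re-intervention) counted to 30 days and 6 months, the 6-month HPA form, and adverse-event reports.

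Conversely, the 6-month wound review is scheduled but matches none of the wound outcomes listed under Secondary outcomes.

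**The case against.** The best counter-argument is that the SSI outcome has two routes, and the CDC route needs no ASEPSIS score on day 90. Antibiotics, primary care visits, readmission and re-intervention are followed to 6 months, and the HPA form is repeated then. Adverse events are recorded from consent until discharge from the trial. An infection that led to admission would count as serious and be reportable within 7 or 15 days. With dates attached, such events could be placed before or after day 90. A reader might infer that neither 90-day outcome can be measured at all; the documents do not support that for the CDC part of SSI.

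This stands, with limits. The article describes no such procedure. Resource use is cut at 30 days and 6 months, not at 90 days. The study-visit items are recorded by an unblinded nurse or doctor, while the blinded assessor has no access to the notes. Adverse-event capture is passive and would miss milder infections. None of it yields an ASEPSIS score, so the healing outcome gains nothing.

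A reader might also infer that the suitability of the outcome measures goes unexamined in implant patients. That goes too far: they have ASEPSIS scores at day 5–7, day 30 and 6 months. Only use at 90 days is untested.

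Finally, these are secondary outcomes in a subgroup of a 144-patient, single-centre pilot. They drive neither the sample size nor the stated success criteria of recruiting a large trial within 18 months and retaining at least 85%. That bears on severity and is accepted. It does not remove the contradiction.

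**Conclusion.** The concern holds as an inconsistency between the outcome list and the assessment schedule. Under the schedule as written, the 90-day healing outcome and the ASEPSIS part of 90-day SSI have no data source. The CDC part has only partial, retrospective and largely unblinded sources. The nearest wound reviews fall at least 57 days before and about 85 days after day 90; the second figure assumes that 6 months is about 182 days.

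The number of implant patients is not given, so the number of infections that might be missed cannot be estimated. The conclusion assumes that implant patients follow the one schedule shown; nothing in the article suggests otherwise.

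Severity: should be fixed. The scheduled 30-day ASEPSIS assessment is unaffected.

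**What to change.** Reconcile Secondary outcomes with Table 1 by one of two routes.

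**Low-cost route.** Restate the 90-day implant outcome as CDC-defined SSI with onset by day 90. Ascertain it from dated records (antibiotics, general-practitioner visits, readmission, re-intervention, adverse events) together with the existing HPA questionnaire, added to the 3-month mailing for implant patients. Drop the 90-day ASEPSIS healing outcome, or move it to the 6-month blinded review that already exists.

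The cost is one extra form in a mailing already planned, dated entries in the case report form, and an amendment to the outcome list and Table 1. The downsides are material:

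- The outcome would rest on records and unblinded self-report. The Sample size calculation section itself reports criticism of questionnaire follow-up and says infections are found more often by a blinded observer.
- The article does not show that the HPA form can establish a CDC diagnosis, so the rule for combining form and records must be written down.
- Recruitment began in January 2017 and was active at publication. Patients already past 3 months could not supply the form.

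The outcome should be labelled as record- and self-report-based wherever it is reported.

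**Route that keeps ASEPSIS at 90 days.** Add a 3-month blinded wound review for implant patients to Table 1 and to the Study visits text. This matches the outcomes as defined and preserves blinding, at the cost of an extra visit with two staff members for each implant patient. It too cannot help patients already past that point.

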### The ASEPSIS scale

The ASEPSIS scale is a standardised tool used to determine the presence of SSI (with a score ≥ 21) or impaired wound healing (score > 10 but < 21) [19]. The ASEPSIS tool has been reported to be repeatable and related to outcome [21, 22]. A score of < 10 is indicative of satisfactory wound healing.

### Quality of life assessments

The EQ-5D questionnaire is a widely recognised and validated generic measure of health-related quality of life. This questionnaire has been assessed for acceptability and validity in a number of patient groups [23, 24]. The SF-36 has been well-validated in a variety of UK populations [25, 26]. It measures eight domains which can be used to calculate summary physical and mental component scores.

### Trial timescales

It is anticipated that the recruitment and treatment phase will be completed within 18 months. The primary endpoint is measured after 30 days, with all patients followed up for 6 months after entry into the trial.

### Sample size calculation

The incidence of SSI’s following clean and clean contaminated, non-implant surgery varies widely between the procedures to be included in this study. Whilst the overall infection rate is quoted as being 2.1–3.3%, this is predominantly based on the findings of Cruse and Foord [27] following their long-term surveillance. This has been criticised as it predominantly relies on questionnaire follow-up, over the phone at day 28 post-surgery. The reality in practice is that the infections rates are much higher and are more frequently diagnosed when examined by a blinded observer [28].

The power calculation is based on the primary endpoint having a 90% power and 5% significance. A non-randomised prospective trial comparing Leukomed® Sorbact® with standard dressings in non-implant, clean or clean-contaminated vascular surgery patients, carried out in the same centre demonstrated an overall reduction in SSI from 19 to 10% [29]. To demonstrate the same reduction in SSI, a sample size of 320 per group, or a total of 712 patients, allowing for a 10% loss to follow-up, is required. Study retention rates will be examined at the first interim analysis, and the power calculation amended accordingly. With such a large sample size, there is a high potential for larger loss to follow-up rates than initially expected. Therefore, this pilot study will aim to recruit one-fifth (144) of the total patients needed. The results of this pilot trial, along with other published data on DACC in the reduction of SSI, will be combined to produce a final power calculation for a full-scale RCT.

### Recruitment

Patients that are referred for a clean or clean-contaminated vascular surgical operation will be considered for the study. Patients may be identified at their initial outpatient appointment, at pre-assessment clinics or on their admission to the ward. Patients admitted on a semi-elective or emergency basis will be identified as they are admitted to the ward. Suitable patients will be made aware of the study and provided with the appropriate information, including the patient information sheet. Following this, patients that express an interest will be invited to a screening visit with a study investigator. For inpatients, this visit may take place on the inpatient ward. At this appointment, patients will be assessed against the inclusion and exclusion criteria, and if potential participants meet said criteria, informed consent to participate in the trial will be taken by a study doctor and recorded on the informed consent form and in the patient notes.

To ensure confidentiality and to adhere to data protection guidelines, participants will be given a unique identifying number which does not allow for the identification of study arms or demographic information. The identifiable patient information will not be available to any person(s) outside of the research group. The patient’s general practitioner will also be informed of study enrolment and study details. No changes to concomitant medications will be made, and no restrictions to trial treatments or methods based on concomitant treatment will be made.

### Randomisation

Consented patients will be randomised to one of the two parallel testing groups (DACC-coated dressing or standard post-operative dressing) by equal randomisation using the online computerised sealed enveloped method (Sealed Envelope, London, UK) (see Fig. 1).

**Fig. 1 Fig1:**
[figure not shown]
Study flow chart. The target sample size for the pilot phase of this study is 144. Treatment and follow-up will run concurrently, giving a total time of 24 months from study start to completion

### Blinding

Due to the nature of the treatment, a double-blind study is not possible (Leukomed® Sorbact® contains a coloured wound contact layer that is not present on standard dressings). To reduce the risk of bias, assessor reported outcomes, namely the ASEPSIS scoring of wounds, will be performed by a blinded assessor who will not have access to the patient notes. Anonymous photos of wounds will be rated by a third blinded assessor to reduce bias and ensure discrepancies in ASEPSIS scores are addressed. Bias in other outcomes will be limited by the use of predetermined objective measurements and bias in quality of life outcomes will be reduced by using patient-reported quality of life outcomes.

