### DACC-coated post-operative dressings and post-operative procedures

Patients will receive standardised care pre-operatively. Hair removal (clipping) and anaesthesia will be conducted according to local hospital policy; in our centre, hair is clipped, not shaven, immediately prior to the procedure in the operating theatre. Skin preparation will be standardised to Povidone-iodine in aqueous solution, unless there is a documented patient allergy. Prophylactic antibiotics will be given as per local guidelines and recorded in the patient notes. Patients will be randomised on the day of their surgical procedure to receive post-operative dressing with a DACC-coated dressing (Leukomed® Sorbact®, BSN Medical, Hull, UK), or a non-coated occlusive absorbent control post-operative dressing (standard practice) (OpSite® Post-Op, Smith & Nephew, Hull, UK).

All dressings will be replaced on day 2 post-procedure, and again at the time of first wound review, which takes place between post-operative days 5–7. Interim dressing changes will be permitted where there is a clinical indication such as soiling or damage to the dressing. On discharge from hospital, patients will be provided with further dressings of the same variety to ensure like-for-like dressing changes up to the point of wound healing, as well as instructions to community teams that the only wound dressings to be used are the ones provided for trial purposes, in order to maintain treatment adherence.

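### Patient self-report and objective measures are offered as bias safeguards for the outcomes not scored blind, but they do not guard against knowledge of the dressing

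*Protocol article*

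**What the plan says.** The Blinding section of the protocol article makes four statements that bear on this point.

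- Allocation cannot be fully concealed: "Due to the nature of the treatment, a double-blind study is not possible". The reason given is that "Leukomed® Sorbact® contains a coloured wound contact layer that is not present on standard dressings".
- Blinded assessment covers the assessor-reported outcomes, "namely the ASEPSIS scoring of wounds, will be performed by a blinded assessor who will not have access to the patient notes". A further blinded assessor rates the wound photographs.
- For the rest, "Bias in other outcomes will be limited by the use of predetermined objective measurements".
- For EQ-5D and SF-36, "bias in quality of life outcomes will be reduced by using patient-reported quality of life outcomes".

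The outcomes outside the blinded scoring are listed under Secondary outcomes. They are EQ-5D and SF-36 at four post-operative times, time to return to normal activity or work, 30-day mortality, and "Resource use—primary care visits, requirement for antibiotics, readmission, re-intervention within 30 days and 6 months".

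**The concern.** The two safeguards sit in the section on blinding, so they read as an answer to the problem that the section has just conceded: people in the trial can tell the dressings apart. Neither safeguard addresses that problem.

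When the patient completes EQ-5D or SF-36, the patient is the outcome assessor. If the patient can recognise the dressing, self-report is the route by which a preference for one product could reach the score. Several of the measures described as objective also start from a decision or an answer given by someone who can see the dressing.

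What is at stake is how these comparisons are read. The Statistical analysis section sets a two-sided 5% significance level and plans between-arm tests of SF-36 (Mann-Whitney), EQ-5D (chi-squared) and time to return to work (log-rank, then Cox regression). A significant difference could be taken as an effect of the dressing when it reflects knowledge of the allocation.

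**Working it through.** **Setting the sections side by side.** The protocol gives no figure for this point, so the main check is a comparison of its sections.

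1. *Can patients recognise the dressing?* The Blinding section says that the products look different. The section on dressings and post-operative procedures has dressings replaced on day 2 and at the first wound review. It then states: "On discharge from hospital, patients will be provided with further dressings of the same variety". Community teams are told to use only the trial dressings. Recognition is therefore very probable, although the protocol never states it outright.
2. *Quality of life.* The patient completes the forms, and the 3- and 6-month questionnaires are postal (Study visits). Staff interpretation is removed; the influence of knowing the dressing remains.
3. *Return to activity.* Study visits has patients asked about driving, exercise and social activity, with the answers recorded by an unblinded nurse or doctor.
4. *Antibiotic use and primary care visits.* These follow from decisions of patients and clinicians who can see the dressing. The same unblinded staff record them.
5. *Readmission and re-intervention.* These are factual events, and Study visits does not name them among the recorded items (its list is only illustrative). The decisions behind them are still open to influence.
6. *30-day mortality.* Objective, and outside the concern.

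**Illustration of what a reporting shift could do.** The assumptions here are mine and are not in the document: no true effect on an EQ-5D item, a proportion p of 40% or 50% of controls reporting problems, and a shift s of 5, 10 or 15 points in one arm caused only by knowing the dressing. The group sizes come from the protocol: 144/2 = 72 per arm in the pilot and 320 per arm in the full trial. The 320 reproduces from 19% versus 10%, two-sided 5%, 90% power, with mean proportion 0.145:

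n = [1.960 × √(2 × 0.145 × 0.855) + 1.282 × √(0.19 × 0.81 + 0.10 × 0.90)]² / 0.09² = 319.6, rounded up to 320. Allowing for 10% loss, 640/0.9 = 711.1, rounded up to 712. The present point does not affect that figure.

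With m = p − s/2, se0 = √(2m(1 − m)/n) and se1 = √([p(1 − p) + (p − s)(1 − p + s)]/n), the chance that the two-sided 5% test rejects is

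Φ((s − 1.96·se0)/se1) + Φ((−s − 1.96·se0)/se1).

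Example with p = 0.40, s = 0.10, n = 72: m = 0.35, se0 = √(0.455/72) = 0.0795, se1 = √(0.45/72) = 0.0791. The first term is Φ(−0.706) = 0.240 and the second is about 0.001, giving 0.241.

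| Shift | 72 per arm, p = 40% | 72 per arm, p = 50% | 320 per arm, p = 40% | 320 per arm, p = 50% |
|---|---|---|---|---|
| 5 points | 9.5% | 9.2% | 25.7% | 24.4% |
| 10 points | 24.1% | 22.5% | 75.7% | 72.1% |
| 15 points | 48.5% | 44.4% | 98.3% | 97.1% |

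Without a shift the rate would be about 5%. A larger trial does not dilute such a shift; it makes a significant result more likely.

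**The case against.** The best reply is that the protocol is already candid. It says that double-blinding is not possible, limits blinded assessment to wound scoring, and calls the recording staff unblinded. It claims only that bias is limited or reduced, not eliminated. Compared with ratings made by unblinded staff, patient completion does reduce one kind of bias. The phrase about objective measurement can be read as covering how an event is recorded, not how the decision behind it is made. On that reading return to work, counted in working days, is a predefined measure, and readmission and re-intervention are facts.

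Much of this stands, and it rules out several stronger readings. A reader might infer that self-report does nothing against bias, or that mortality is the only objective outcome; the text supports neither. A reader might infer that patients are known to be unblinded, but this is an inference from the visible difference and the supply taken home. Nor does the Statistical analysis section state a between-arm test for resource use, so the point about p < 0.05 applies to quality of life and return to work. The patient information sheet is not shown, so nothing can be said about how it describes the dressings.

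What the reply does not meet is the core. In a section on blinding, the relevant bias is that from knowing the allocation, and the measures named for these outcomes do not reduce it.

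**Conclusion.** The concern holds as a modest point about a stated safeguard. Patient reporting removes rater bias from EQ-5D and SF-36 but leaves expectation bias. Objective measurement does not describe return to activity, antibiotic use or primary care visits well, and it covers only the occurrence of a readmission or re-intervention, not the decision that led to it.

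The conclusion assumes that patients and the clinicians treating them usually recognise the dressing, which the protocol makes very likely without saying so. Neither the direction nor the size of any bias can be derived from the document, and the rejection rates above depend wholly on assumed shifts. The consequence is limited: these are secondary outcomes in a pilot of 144, the future power calculation concerns surgical site infection, and the blinded ASEPSIS scoring and mortality are unaffected. It is still worth correcting, because quality of life and return to work are to be tested between arms at the 5% level.

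**What to change.** - **Blinding section.** Replace the two claims with a statement to this effect: only ASEPSIS scoring, including the photograph rating, is assessed blind; mortality is objective; quality of life, return to activity and resource use are open-label. It can fairly add that patient completion avoids interpretation by staff but not the influence of knowing the dressing.
- **Statistical analysis section.** Report between-arm differences in these open-label outcomes as estimates with confidence intervals, and say that no conclusion about effectiveness will be drawn from p < 0.05.
- **Optional.** Report antibiotic courses given for the study wound separately from other courses. This is a small refinement of the definition and is not needed for the main point.

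The cost is a few sentences of wording and, if the option is taken, a record of the indication for each antibiotic course. Treatment, sample size and the infection analysis do not change. The downside is a weaker claim for these secondary outcomes.
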